## 5. Power and Statistical Analysis

The investigator will be responsible for the data analysis. The analysis will be performed on a blinded data set after medical/scientific review has been completed and all protocol violations have been identified and the data set has been declared complete.

There are two primary end-points: The Leiden Surgical rating Scale (see table above) and postoperative pain. The hypothesis of the study is that a deep neuromuscular block will coincide with improved surgical conditions as compared to a standard of care block and less postoperative pain.

Secondary end-points include: hemodynamics during surgery (blood pressure, heart rate); and sedation/SpO2/blood pressure/heart rate in the recovery period. The hypotheses are: Deep block coincides with optimal hemodynamic conditions during surgery; Deep block coincides with less pain in the recovery room albeit without any cardiorespiratory compromise.

**Sample size: Powering the study on Surgical Rating Scale:** The estimated mean difference between the treatment groups is conservatively estimated to be at 0.5 (but probably > 1), and combined with various assumptions on the variability (that is anticipated to be approximately 0.4), a sample size of 20 per group would provide at least 90% power to observe the expected difference (see table below):

MEAN DIFFERENCE between treatments

|      | SD 0.4    | SD 0.45   | SD 0.5    |
|------|-----------|-----------|-----------|
| 0.4  | 23        | 28        | 34        |
| 0.45 | 18 | 23        | 27        |
| 0.5  | 15        | 19 | 23        |
| 0.55 | 13        | 16        | 19 |
| 0.6  | 11        | 13        | 16        |

Table: Sample size per group by range of mean group differences and standard deviations (SD) at 90% power.

**Powering postoperative pain:** Assuming a difference in pain score between the two treatment groups of 1.0 (numerical ratings scale), a SD of 1.5 (CV 150%), and alpha of 0.05, the study has a power > 0.9 to detect a difference with 100 subjects. We therefore decided to enrol 100 patients (50 per group) in this study allowing the detection of a difference in Surgical rating Scale and pain in the recovery room. This approach ensures adequate power to detect significant and clinically relevant differences in the surgical rating scale and postoperative pain. We expect no difference in PQRS, sedation and respiratory parameters.

Statistical analysis will be by analysis of variance or t-test as specified by Martini et al. Br J Anaesth 2014. Descriptive and inferential statistics were used for analysis. All data are first tested for normality by a Q-Q plot, a Kolmogorov-Smirnov and a Levene's test.

Descriptive statistics are used to outline characteristics of included patients. Continuous normally distributed variables are expressed by their mean and standard deviation, not normally distributed data by their median and range. To test groups, categorical variables are tested using the Pearson's Chi-square test or Fisher's exact test, when appropriate. Normally distributed continuous data are tested with Students t-test and in case of skewed data, with the Mann-Whitney U test.

**Amendment:** After consultation with a statistician we decided to analyze the Surgical Rating Scale and the pain score as continuous variables, as we are dealing with at least 5 categorical scales (see Martini et al., 2014). Statistical analysis on the Surgical Rating Scale and pain score in the post anesthesia care unit will then be by linear-mixed model with an autoregressive covariance structure. *Post hoc* analysis was by t-test (with  $p < 0.01$  considered significant). Pain scores on the ward (wound pain, deep pain shoulder pain) will be averaged and the group comparison will be by t-test.

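### Levene's test is listed as a test of normality, so the wording invites moving normal data with unequal spread to Mann-Whitney, and no unequal-variance t-test is offered (minor; secondary continuous outcomes only)

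*Protocol*

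**What the plan says.** All the relevant text is in Protocol section 5, Power and Statistical Analysis.

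- **Preliminary tests:** "All data are first tested for normality by a Q-Q plot, a Kolmogorov-Smirnov and a Levene's test".
- **Choice of summary:** "Continuous normally distributed variables are expressed by their mean and standard deviation, not normally distributed data by their median and range".
- **Choice of test:** "Normally distributed continuous data are tested with Students t-test and in case of skewed data, with the Mann-Whitney U test".
- **Amendment, primary outcomes:** "Statistical analysis on the Surgical Rating Scale and pain score in the post anesthesia care unit will then be by linear-mixed model with an autoregressive" (the quote is cut short; its last word describes the covariance).
- **Amendment, ward pain:** the scores "will be averaged and the group comparison will be by t-test".

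The section does not say how the three preliminary checks are combined, or what follows if they disagree. It names no t-test for unequal variances. Its analysis text also opens with a general reference to analysis of variance or t-test as in an earlier published trial, without saying which outcomes that covers.

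**The concern.** Levene's test asks whether groups have the same variance. Two perfectly normal samples with different spread will fail it, and two badly skewed samples with similar spread can pass it. Listing it as a normality test is an error on the face of the text.

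The error can have a consequence because the normality result selects both the summary and the test. An analyst who takes the list at its word may read a Levene rejection as a failure of normality, and the only other branch is median and range with Mann-Whitney. The comparison then no longer addresses a difference in means, and the switch was triggered by something that is not non-normality. The one problem that Levene's test can detect, unequal variance, has no matching remedy in the plan. Two analysts following the same paragraph could choose different tests for the same variable after seeing the data.

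Unequal spread is plausible for some affected outcomes. Under section 4 the arms differ by design in rocuronium and sugammadex dosing, and drug doses and time to TOF ratio > 0.9 are recorded.

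**Working it through.** **1. Which outcomes are affected.** The amendment fixes a mixed model for the surgical rating scale and PACU pain, and a t-test for averaged ward pain. None of these passes through the preliminary tests. Still under the rule are time to TOF ratio > 0.9 and drug doses (section 4). The secondary haemodynamic, SpO2 and sedation outcomes (section 5) are under it only where a two-group test is used. Sections 3 and 4 have them recorded repeatedly, so analysis of variance may govern them instead.

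**2. The plan's own figures.** For pain, section 5 assumes a difference of 1.0 and "a SD of 1.5 (CV 150%), and alpha of 0.05, the study has a power > 0.9 to detect a difference with 100 subjects". With 50 per group and a two-sided test (sidedness is not stated):

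- Standard error = 1.5 × √(2/50) = 0.30
- Power = Φ(1.0/0.30 − 1.96) = Φ(1.37) = 0.915; the noncentral t gives 0.910

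The stated power above 0.9 reproduces. All 15 cells of the rating-scale table also reproduce with a two-sided t-test at 90% power. The sample size is not in question.

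**3. What the misreading would do to normal data.** Suppose Levene's test (mean-centred, 0.05 level) sends the comparison to Mann-Whitney when it rejects and to Student's t when it does not. The simulation used normal data, 50 per arm and 20,000 replicates. The unequal SDs are assumptions, since the protocol gives none.

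| SDs | Ratio | Levene rejects | Type I error, this rule | Student | Welch |
|---|---|---|---|---|---|
| 1.5, 1.5 | 1 | 5% | 0.051 | 0.051 | 0.051 |
| 1.5, 2.0 | 1.33 | 45% | 0.053 | 0.054 | 0.054 |
| 1.5, 2.25 | 1.5 | 74% | 0.052 | 0.051 | 0.050 |
| 1.5, 3.0 | 2 | 99% | 0.057 | 0.049 | 0.048 |

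Power at a difference of 1.0:

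| SDs | This rule | Welch | Loss |
|---|---|---|---|
| 1.5, 1.5 | 0.909 | 0.910 | 0.1 points |
| 1.5, 2.25 | 0.708 | 0.726 | 1.8 points |
| 1.5, 3.0 | 0.521 | 0.543 | 2.2 points |

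**4. Isolating Levene's test.** A second simulation (4,000 replicates) put Kolmogorov-Smirnov, with parameters estimated in each arm, into the rule as well. At SD ratios 1.5, 2 and 3, type I error was 0.048, 0.056 and 0.067 with Levene's test in the rule, and 0.047, 0.055 and 0.052 without it. Repeat runs put the ratio 3 figure as high as 0.072. Levene's test makes a material difference only at ratio 3.

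**The case against.** The strongest objection is that the protocol contains no diversion rule. Mann-Whitney is assigned "in case of skewed data, with the Mann-Whitney U test", and normally distributed data are assigned to the t-test. Normal data with unequal spread are not skewed, so read literally they stay with the t-test. The sentence may simply be a loosely worded list of t-test assumption checks. This stands: diversion on Levene's test alone is a reading that the wording invites, not a stated rule. The mislabelling remains, as does the lack of any statement on how the three checks combine.

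A reader might also infer that the rule badly inflates false positives. With skewed data of equal mean but different shape (gamma shape 1.5 or 1 against 4, assumed), a rule with Levene's test included rejects in 16.6% or 36.0% of trials. Removing Levene's test leaves 16.7% or 36.0%. The excess comes from applying Mann-Whitney to data that truly are skewed and truly differ in distribution. It counts as error only if the target is a difference in means, and the protocol summarises non-normal data by the median. These figures are no evidence against the use of Levene's test.

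Finally, pre-testing is a common convention, and test choice for secondary outcomes is often left to an analysis plan, which may exist here. That is a fair answer to a demand that all pre-testing be dropped. It does not excuse a sentence that the protocol states wrongly.

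**Conclusion.** The point holds as a minor methods error. Levene's test is not a test of normality, the sentence invites a wrong switch of summary and test, and the plan offers no t-test suited to unequal variances.

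The effect is small. Under the assumed SD ratios and 50 per arm, most normal data sets with clearly unequal spread would be flagged. Type I error would still stay at about 0.05 up to ratio 2 and reach about 0.07 at ratio 3, with about 2 points of power lost against Welch's test. With equal arms Student's test also keeps its level up to ratio 2 (0.049 to 0.054), so the missing Welch option costs little while the arms stay balanced. The main damage is ambiguity: the test and summary for a secondary outcome could be settled after the data are seen.

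The documents do not support reading this as a threat to the primary comparisons or to every other continuous outcome. Both primary endpoints and ward pain are outside the rule, and no sample size changes.

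**What to change.** Change the paragraph in section 5 as follows:

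- Describe Levene's test only as a check of equal variance, and remove it from the normality decision.
- For single-measurement continuous outcomes compared on means, use Welch's t-test and report the mean difference with a 95% confidence interval.
- Keep Mann-Whitney for outcomes named in advance as skewed.

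This is about two sentences of text. Welch's test costs essentially no power when spreads are equal (0.910 for both Welch and Student in the simulation). Sample size, primary analyses and data collection are unchanged.

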#### **Amendment: Comparison of the Leiden Surgical Rating Scale among surgeons**

In order to get an indication of the validity of the Leiden Surgical Rating Scale among surgeons we will add a third post hoc group of 50 patient that will receive standard of care, ie. just one 30 mg rocuronium infusion dose at the beginning surgery. This will lead to three NMB groups (single dose, moderate NMB and deep NMB). For each of the surgeons that will participate in the study (currently it is expected that three surgeon will participate) we will create a dose-response relationship of dose (the level of NMB) vs surgical rating scale. We will assess 1) whether dose dependency is observed for the surgeons and 2) whether the variability (with-in observer variability) in the data is similar among the surgeons.

